### Primary outcomes

The primary outcome is postoperative delirium. The diagnosis of postoperative delirium will be based on using the Confusion Assessment Method (CAM) [2]. CAM has been validated against the Diagnostic and Statistical Manual Disorders Fourth Edition. All patients will be evaluated for delirium with the CAM 2 times daily, for 72 h or until discharge if the hospital stay is <72 h, by trained research assistants. These assessments will be done on post-operative nights 1, 2 and 3 or until discharge (if the hospital stay is <72 h), with at least 6 h between assessments. The first assessment for delirium will be performed when patients can be sufficiently aroused (Richmond Agitation and Sedation Score > −4) [38] in order to be assessed for delirium on the day of surgery [39, 40]. If the patient’s delirium persists beyond 72 h after surgery, he/she will be assessed with the CAM twice daily until the delirium resolves.

### Secondary outcomes

The secondary outcome measures include: length of stay, time to ambulate, perioperative complications {i.e. intensive care unit admission, hypoxia (SpO_2_ < 90%), re-intubation, myocardial infarction/ischemia, wound infection, deep vein thrombosis, pulmonary embolus, pneumonia, urinary tract infection, sepsis, stroke, etc.} occurring within 30 days after the surgical procedure.

### Standardization of training

All study research assistants who perform the assessments for delirium will be trained by a staff psychiatrist at University Health Network to administer the CAM. The research assistants will also attend a delirium training session for CAM offered at University Health Network. Once the trainees have met the requirements of their training, they will each conduct their first interview in the presence of a previously trained team member on a patient enrolled in the study.

### Adherence

Patients in the intervention group will be reminded in each study visit the importance of adherence to APAP therapy.

### Retention and withdrawal

Each study site will make every effort to maintain interest by supporting their participants throughout the perioperative period. Participants may withdraw from the study for any reason at any time.

### Sample size

Based on an expected incidence of postoperative delirium of 24% in untreated OSA patients and 9.9% in treated OSA patients [11, 18] assuming a power of 0.8 and alpha error of 0.05, 110 patients/group (220 in total) are required. If the dropout rate is 20%, 264 patients need to be randomized. In our previous study, 45.9% of patients who had PSG met AHI criteria for OSA [41]; therefore, to obtain 220 patients with OSA, we need 576 patients to successfully complete the sleep study. If we assume that the rate of withdrawal and testing failure is 10%, we need to recruit a total of 634 patients for ApneaLink™ Air testing.

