**Methods:**

This multi-centre randomized controlled trial will enrol 634 elderly patients undergoing elective hip/knee replacement surgery. The study has been approved by the Research Ethics Boards of the three participating institutions. Patients will be screened with the STOP-Bang questionnaire. Those with a score of 3 or greater will have a portable home sleep study using the ApneaLink™ Air device. Patients identified to have OSA will be randomized to 1) Auto-titrating continuous positive airway pressure (APAP) applied during sleep for 72 h after surgery or until discharge if they are discharged before 72 h **or** 2) Control group – routine care, no APAP. All patients will be evaluated for delirium for 72 h after surgery or until discharge if they are discharged before 72 h. The primary outcome is the occurrence of delirium – assessed twice daily using the Confusion Assessment Method for 72 h or until discharge if the hospital stay is <72 h.

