## Methods

### Trial design

The **P**revention **O**f **D**elirium in **E**lderly with Obstructive **S**leep **A**pnea (PODESA) study is a multi-centre, prospective, randomized controlled superiority trial with two parallel groups. Randomization at each site will be performed with a 1:1 allocation into intervention (APAP) or control (routine care) group. The overall study design is shown in Fig. 1.

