### Data and statistical analysis

The primary outcome - the incidence of postoperative delirium in the APAP and control group will be compared and the significance of the difference will be assessed with Chi-square test. The secondary outcomes that will be compared between the two groups include: length of stay, time to ambulate, intraoperative and postoperative complications (i.e. respiratory, cardiovascular, death, etc.). An intention-to-treat and a per-protocol analysis will be used to compare the intervention (APAP) vs. control (routine care) group. Differences in the primary and secondary outcomes will be assessed using parametric and non-parametric tests where appropriate, and a *P*-value <0.05 will be considered statistically significant. SAS 9.3 will be used to perform the statistical analyses.

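### The sample-size section adds its loss allowances by multiplying instead of dividing and mislabels one number, so 264 randomised and 634 recruited give about 210 evaluable patients and about 78% power, slightly below plan

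*Protocol article*

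**What the plan says.** All the steps are in the Sample size section of the protocol article. The section starts from an "expected incidence of postoperative delirium of 24% in untreated OSA patients and 9.9% in treated OSA patients" and concludes, "assuming a power of 0.8 and alpha error of 0.05, 110 patients/group (220 in total) are required". Three steps follow:

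- Dropout: "If the dropout rate is 20%, 264 patients need to be randomized".
- OSA yield, at 45.9% from the team's previous study: "therefore, to obtain 220 patients with OSA, we need 576 patients to successfully complete the sleep study".
- Withdrawal and failed tests: "If we assume that the rate of withdrawal and testing failure is 10%, we need to recruit a total of 634 patients".

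The Methods part of the abstract repeats the last figure as the trial's size: "This multi-centre randomized controlled trial will enrol 634 elderly patients undergoing elective hip/knee replacement surgery". Allocation is 1:1 (Trial design), and for the primary outcome "the significance of the difference will be assessed with Chi-square test" (Data and statistical analysis).

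**The concern.** The base requirement has no reserve. By the usual formula, 110 per group is the smallest number that reaches 80% power, so the later steps must deliver 220 evaluable patients for the power statement to hold. An allowance for a loss fraction d has to divide by 1 − d, because the loss is taken from the larger number. The section multiplies by 1 + d at both loss steps, so each target falls short of the number it is meant to protect, and the two shortfalls compound.

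The yield sentence raises a different problem. It says that 576 completed sleep studies will produce 220 patients with OSA. The sentence before it calls for 264 to be randomised, and 576 fits 264, not 220.

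At stake are the stated power and a headline recruitment figure that the abstract repeats. Design, analysis and patient safety are not affected.

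**Working it through.** **Inputs (Sample size section unless noted).** Delirium 24% untreated and 9.9% treated; power 0.80; alpha 0.05; dropout 20%; OSA yield 45.9%; withdrawal and testing failure 10%; 1:1 allocation (Trial design); chi-square test (Data and statistical analysis). The article does not say whether alpha is one- or two-sided. I assume two-sided because that reproduces the plan's figure; one-sided gives 87 per group.

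**Base step.** Pooled two-proportion formula without continuity correction, with mean proportion (0.24 + 0.099)/2 = 0.1695 and difference 0.141:

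- n = [1.96 × √(2 × 0.1695 × 0.8305) + 0.8416 × √(0.24 × 0.76 + 0.099 × 0.901)]² / 0.141²
- n = 109.96, so 110 per group and 220 in total. This matches the plan, and power at 110 per group is 80.0%.

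**How the stated figures arise, and what each should be.**

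| Step | Stated | How it arises | Consistent on its own | Consistent, cumulative |
|---|---|---|---|---|
| Randomised | 264 | 220 × 1.2 | 220 / 0.8 = 275 | 275 |
| Completed sleep studies | 576 | 264 / 0.459 = 575.2, rounded up | 576 (correct for 264) | 275 / 0.459 = 599.1, so 600 |
| Recruited | 634 | 576 × 1.1 = 633.6 | 576 / 0.9 = 640 | 600 / 0.9 = 666.7, so 667 |

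**Yield sentence.** 576 × 0.459 = 264.4. Obtaining 220 would take 220 / 0.459 = 479.3, so 480 completed studies. The number carried forward is right for 264; only the label 220 is wrong.

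**What 634 recruited delivers at the plan's own rates.**

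- Completed sleep studies: 634 × 0.9 = 570.6
- With OSA and randomised: 570.6 × 0.459 = 261.9
- Evaluable after 20% dropout: 261.9 × 0.8 = 209.5, about 105 per group

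The shortfall against 220 is 10.5 patients. The dropout step accounts for most of it: 264 × 0.8 = 211.2, which is 8.8 short. The recruitment step adds the other 211.2 − 209.5 = 1.7.

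**Power at those numbers.**

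| Evaluable per group | Pooled formula | Exact enumeration, uncorrected chi-square |
|---|---|---|
| 110 (as required) | 80.0% | 81.2% |
| 105 (as delivered) | 78.1% | 79.3% |

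**Read the other way.** 264 leaves 220 only if dropout is 44/264 = 16.7%, and 634 leaves 576 only if the loss is 58/634 = 9.1%. The text states 20% and 10%.

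**The case against.** The strongest reply is that this hardly matters. Power falls about 2 points by the plan's formula, and by exact enumeration it ends only 0.7 points under 80%. The assumed delirium rates, dropout and OSA yield are all uncertain, and modest errors in them could outweigh this gap. Taken alone, the recruitment step is a difference of six people tested (640 against 634). All of that stands, and it limits the severity. It does not make the figures consistent with the loss rates printed beside them.

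A second reply is that dropouts need not be lost to the primary analysis, since the article plans an intention-to-treat as well as a per-protocol comparison. The article does not say how dropouts are handled, so 210 evaluable is what the plan's own allowance implies and not a certain outcome. But the section adds the allowance precisely because it expects to lose those patients, and the allowance is calculated wrongly on that footing.

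A reader might also infer that the section sets two randomisation targets, 220 and 264, and that a team could stop at 220. That would leave 220 × 0.8 = 176 evaluable, 88 per group, with power about 71%. The document does not support this reading. It says outright that 264 are to be randomised, and the recruitment figure of 634 is built from 264. Nothing makes 220 a stopping point, and the Data monitoring section provides for stopping only on safety grounds. The 220 in the yield sentence is a wrong label.

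**Conclusion.** The point holds as two inflation errors and one mislabelled number. At the plan's own rates, 264 randomised and 634 recruited fall about 10 evaluable patients short of the required 220. Power is about 78% by the pooled formula, or about 79% by exact enumeration, against the stated 80%. The consistent chain of 275, 600 and 667 exceeds the stated 264, 576 and 634 by 4.2%, 4.2% and 5.2%.

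This rests on a two-sided alpha of 0.05, on the plan's event rates, and on dropouts being lost to the primary comparison, as the allowance implies. The base figure of 110 per group is correct. The mislabelled 220 contributes nothing to the shortfall, so it would be wrong to count three causes.

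Severity is minor to should-fix. The statement of size and power is wrong as written, but the primary conclusion is not threatened.

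**What to change.** Two edits in the Sample size section are enough:

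1. Keep 264 and 634, and state that at 10% testing loss, 45.9% OSA yield and 20% dropout, 634 recruited is expected to give about 262 randomised and about 210 evaluable patients, with about 78% power for 24% against 9.9%. Say that alpha is two-sided, if that is what was meant.
2. In the OSA-yield sentence, replace 220 with 264.

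This costs a few sentences. Nobody extra is enrolled, the abstract's 634 can stay, and the only concession is a slightly lower stated power.

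If the sponsor prefers to hold 80% power at the stated loss rates, the targets become 275 randomised, 600 completed sleep studies and 667 recruited. That means 11 more randomised, 24 more completed studies and 33 more recruited. The yield sentence would then name 275, and the abstract's figure would have to change. This is a choice about resources and is not needed to put the text right.

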### Data and statistical analysis

The primary outcome - the incidence of postoperative delirium in the APAP and control group will be compared and the significance of the difference will be assessed with Chi-square test. The secondary outcomes that will be compared between the two groups include: length of stay, time to ambulate, intraoperative and postoperative complications (i.e. respiratory, cardiovascular, death, etc.). An intention-to-treat and a per-protocol analysis will be used to compare the intervention (APAP) vs. control (routine care) group. Differences in the primary and secondary outcomes will be assessed using parametric and non-parametric tests where appropriate, and a *P*-value <0.05 will be considered statistically significant. SAS 9.3 will be used to perform the statistical analyses.

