## Background

### Postoperative delirium

Delirium is an acute confusional state, with fluctuating impairment in attention and decreased awareness of one’s environment [1, 2]. Postoperative delirium is a common complication after major surgery; the incidence has been reported to be 13–41% after elective hip or knee replacements, and 26–61% for patients undergoing femoral neck fractures [3, 4]. Postoperative delirium is associated with increased mortality, morbidity, longer hospital stays [5], higher hospital costs [6], cognitive deterioration, and delayed rehabilitation. The pathophysiology of delirium remains poorly understood. The development of postoperative delirium is thought to be a multi-factorial process [7] with a combination of predisposing and precipitating factors. Predisposing factors can be defined as the patient’s baseline vulnerabilities and precipitating factors as injury that occurs throughout the perioperative period [8]. Predisposing factors include sex, age, cognitive status, and coexisting medical conditions, while precipitating factors include surgery, and hypoxia, however, there are few effective preventive measures for delirium [9]. The clinical presentation of delirium varies [10] but postoperative delirium typically occurs on days 2 and 3 after surgery [11, 12].

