### Study setting

This ongoing study is being conducted at three academic hospitals: Toronto Western Hospital, University Health Network; Mount Sinai Hospital; and Sunnybrook Hospital located in Toronto, Ontario Canada over 3 years. The target completion date is December 2018.

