### Patient screening and baseline assessment

Trained research assistants will screen patients who are scheduled for elective hip or knee replacement surgery in each site for eligibility to participate in the study. There will be no financial or non-financial incentives provided to participants for enrolment. Those interested in participating in the study will be given written information about the study, including the objectives and procedures. Research assistants will ask patients to provide written informed consent prior to collection of the baseline assessment.

In the preoperative clinics, all patients who consent will complete the STOP-Bang questionnaire [29, 30], Epworth Sleepiness Scale [31], Charlson comorbidity index [32], and Mini-Cog Test [33, 34]. The STOP- Bang Questionnaire is a validated questionnaire to screen patients for OSA [29]. If a patient has a STOP-Bang score of 3 or higher, they will have a portable home sleep study with ApneaLink™ Air (ResMed, San Diego, California, USA) for one night. ApneaLink™Air is a Type III sleep apnea monitoring device that records the following data: nasal airflow, snoring, blood oxygen saturation, pulse and respiratory effort during sleep.

The sleep data will be manually scored and checked by a qualified sleep technologist, and interpreted by the study sleep physician for recordings of at least 3 h duration. In the case of inadequate sleep or any technical failure, the patient will repeat the Apnea LinkAir™ study once. The conduct, data retrieval and interpretation of the sleep study will be guided by the current Canadian Sleep Society [35] and American Academy of Sleep Medicine [36] guidelines for portable monitors. The scoring criteria for breathing events will be guided by the American Academy of Sleep Medicine definition [37]. An apnea is defined as a decrease in airflow by ≥90% of baseline for ≥10 s. A hypopnoea is defined as a decrease in airflow by >30% baseline for ≥10 s in association with either ≥3% oxygen desaturation from pre-event baseline and/or the event is associated with an arousal [37].

Oximetry monitoring with a high-resolution pulse oximeter wristwatch (PULSOX-300i, Konica Minolta Sensing, Inc., Osaka, Japan) will be carried out for one night before surgery and for three nights postoperatively or until discharge if the hospital stay is <72 h.

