### Assignment of interventions

A computer generated randomization list for each participating site will be created by a research analyst who is not involved in the study. The patient assignments will be placed in serially numbered, opaque-sealed envelopes corresponding with the randomization schedule for each site. The research assistant will open the envelope after the sleep study confirms the diagnosis of OSA for the patient.

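### The named primary test, an unadjusted chi-square, is valid and meets the planned power, but a prespecified analysis adjusted for site, age and Mini-Cog would use the site-wise allocation and baseline data for a small gain at little cost

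*Protocol article*

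**What the plan says.** Protocol article, Data and statistical analysis: the incidence of delirium in the two arms "will be compared and the significance of the difference will be assessed with Chi-square test". The only other wording on tests in that section is general: "Differences in the primary and secondary outcomes will be assessed using parametric and non-parametric tests where appropriate". It names no stratified or covariate-adjusted method.

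Trial design: "Randomization at each site will be performed with a 1:1 allocation into intervention (APAP) or control (routine care) group". Under Assignment of interventions, the article adds how the lists are made: "A computer generated randomization list for each participating site will be created by a research analyst who is not involved in the study". Study setting gives three hospitals. Site is therefore a factor in the allocation. The article does not give block sizes.

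Background, Postoperative delirium: "Predisposing factors include sex, age, cognitive status, and coexisting medical conditions". No effect sizes are given.

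Patient screening and baseline assessment: "In the preoperative clinics, all patients who consent will complete the STOP-Bang questionnaire", together with the Epworth scale, the Charlson index and the Mini-Cog. The allocation envelope is opened only after the sleep study has confirmed sleep apnea, so these are all pre-randomisation measurements. Age is known for every patient because it is an eligibility criterion.

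**The concern.** When allocation is arranged within sites, the natural analysis also compares the arms within sites. A pooled chi-square counts between-site differences in delirium as noise and becomes slightly conservative if those differences are large. Likewise, adjusting a binary outcome for baseline variables that predict it usually raises power, and the article already collects such variables.

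What is at stake is precision. The trial is sized for exactly 80% power at a large assumed effect (24% to 9.9%), and few events are expected. An inexpensive gain is worth having, and it is credible only if the covariates are named in advance. The point rests on the primary test that the article does name. It does not rest on the absence of supportive analyses, which may stand in a full protocol or SAP that is not shown.

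**Working it through.** **1. The plan's own figure.** Inputs from Sample size: p1 = 0.24, p2 = 0.099, alpha 0.05 (taken as two-sided), power 0.80. The pooled-variance formula, which matches an uncorrected chi-square, is

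n = [1.960·√(2p̄q̄) + 0.842·√(p1q1 + p2q2)]² / (p1 − p2)²

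- p̄ = (0.24 + 0.099)/2 = 0.1695, so √(2 × 0.1695 × 0.8305) = 0.5306.
- √(0.24 × 0.76 + 0.099 × 0.901) = √0.2716 = 0.5212.
- n = (1.0400 + 0.4386)² / 0.141² = 2.186/0.01988 = 110 per group.

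The stated 110 reproduces. Power at 110 per group is 80.0% by formula and 81.2% by exact enumeration. The sample size was computed for the test that is named.

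**2. Expected events.** 110 × 0.24 + 110 × 0.099 = 26.4 + 10.9 = 37.3. Treatment, two site indicators, age and Mini-Cog make five parameters: 37.3/5 = 7.5 events per parameter.

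**3. Simulation.** N = 220 and marginal risks held at 24% and 9.9%, with 4,000 runs per scenario (Monte Carlo standard error of power about 0.6 points). Assumed, because the article does not give them: site shares 45/30/25%, permuted blocks of 4 within site, site differences, and one standard-normal baseline score standing for the combined prognostic content of the covariates. The adjusted test is the likelihood-ratio test for treatment in a logistic model with site and the score.

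Power with no site differences:

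| Assumed log OR per SD | Chi-square | Adjusted | Gain (points) |
|---|---|---|---|
| 0 | 80.2% | 80.5% | 0.3 |
| 0.5 | 80.4% | 82.6% | 2.2 |
| 0.8 | 81.1% | 84.6% | 3.5 |
| 1.2 | 80.2% | 87.2% | 7.0 |

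As an equivalent sample size, [(1.96 + z for adjusted power)/(1.96 + z for chi-square power)]²:

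- 0.5: (2.898/2.816)² = 1.06
- 0.8: (2.979/2.842)² = 1.10
- 1.2: (3.096/2.809)² = 1.21

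That is about 6%, 10% and 21% more patients.

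Site alone (Mantel-Haenszel by site against chi-square, no covariate effect):

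- No site differences: 79.9% against 80.2%.
- Site log odds at 0 and ±0.8: 81.1% against 80.2%.
- A separate run of 1,500 trials with a spread of ±1, which is a 7.4-fold odds ratio (e²) between the extreme sites: 82.8% against 80.7%.

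Type I error over the eleven combinations of site and covariate effect completed: chi-square 4.0-5.1%, adjusted test 4.9-5.7% (Monte Carlo standard error about 0.3 points). The 4.0% arose with site log odds at ±0.8.

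**4. Sensitivity to the set-up.** Other simulations of the same comparison gave gains of about 3 to 5 points for log odds ratios of 0.7 to 1.0, and about 1 to 4 points for 0.5 to 1.0. The direction agrees. The size depends on the assumptions.

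**The case against.** The strongest case against is that nothing is wrong. The test matches the sample size calculation, holds its level and delivers the planned power. That stands, and it rules out several stronger readings that a reader might infer:

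- **That ignoring the site lists invalidates the test.** It does not. The effect on type I error is nil or slightly conservative. If the lists use simple rather than blocked randomisation, even the conservatism disappears.
- **That the trial is underpowered because of the chi-square.** It is not. What is forgone is a gain above 80%. The dropout allowance is a separate matter: 264 × 0.8 = 211 patients would leave about 78% power, whatever one thinks of the test.
- **That the baseline predictors are strong.** The article names predisposing factors and gives no strength. Eligibility excludes dementia and clinically significant neurological disease, requires cognitive capability and sets age at 60 or over. Mini-Cog and age may therefore predict less here than in unselected patients, which points to the lower part of the range.
- **That chance imbalance biases the result.** Randomisation covers chance imbalance in the chi-square's error rate. Adjustment improves precision and does not remove a bias.
- **That site differences matter much.** The three hospitals are in one city, do the same elective operations and share CAM training. Nothing suggests the spread needed for even a 2-point gain.

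It is also fair that adjustment has a price: about 7 events per parameter, and a likelihood-ratio test whose simulated level reached 5.7%. This is small, but it argues for a short covariate list and one clearly designated primary P-value.

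The objection does not remove the core. The article fixes the primary test as unadjusted and gives no role to site or to baseline data it already holds.

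**Conclusion.** The point holds as a modest efficiency improvement. The chi-square is valid, at most slightly conservative, and meets the planned 80% power at 110 per group. Adjustment would add about 0 to 7 points of power over assumed log odds ratios per SD of 0 to 1.2. Almost all of that comes from the covariates. Site alone adds about 0 to 1 point, and at most about 2 if sites differ strongly. If the covariates turn out not to be prognostic, little or nothing is lost. These sizes rest on assumed predictor strength, site shares, site differences and blocking, none of which the article gives.

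**What to change.** Replace the primary-analysis sentence with text along these lines:

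*The primary analysis is a logistic regression of delirium (yes/no) on treatment group, adjusted for site, age and Mini-Cog score, with age and Mini-Cog each entered as one linear term. The likelihood-ratio P-value for treatment is the single primary test. The primary estimate is the standardised risk difference with its 95% confidence interval; the adjusted odds ratio is reported alongside. If the model does not converge, a Cochran-Mantel-Haenszel test stratified by site is used instead. The unadjusted chi-square is supportive.*

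Do not extend the covariate list: with about 37 events, five parameters already leave only about 7 events each. Because the trial is under way, record the change as a dated amendment, made without sight of delirium results by arm, including those in the planned interim safety review.

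Cost: about one paragraph of text and a slightly more complex model. The sample size is unchanged and no new data are needed.
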